### Outcomes

Table 
1 provides an overview of the data collected during the trial. Baseline assessments will take place several days to several hours preoperatively, depending on usual logistic procedures in the participating hospitals. Follow-up measurements will take place at three days and 3, 6, 9, 12 and 26 weeks postoperatively. The study will use standardised instruments with demonstrated validity, reliability and responsiveness. Outcomes will be measured using online questionnaires, but postal questionnaires are available if requested. The baseline measures will include demographic data (such as age, gender and education), relevant prognostic factors and both primary and secondary outcomes.

**Table 1 T1:** Overview of the data collection

**Outcome measures**		**Follow-up**						
	**Baseline**	**3 days**	**1 wk**	**3 wk**	**6 wk**	**9 wk**	**12 wk**	**26 wk**
Demographic data	X							
***Primary outcomes***								
Functional status (ODI)	X			X	X	X	X	X
Pain intensity leg (NRS)	X	X		X	X	X	X	X
Pain intensity back (NRS)	X	X		X	X	X	X	X
Global perceived recovery (GPE)				X	X	X	X	X
General health status (SF-12)	X			X	X	X	X	X
Health related quality of life (EQ-5D)	X			X	X	X	X	X
***Secondary outcomes***								
Psychosocial status (ÖMPSQ)	X							
Fear avoidance beliefs (FABQ)	X							
Expectations (CEQ)	X		X					
Pain Coping (PCI)	X							
***Prognostic factors***								
Length/severity of complaints	X							
Surgical complications		X						
***Economic evaluation***								
Absence from work (PRODISQ)					X		X	X
Cost questionnaire					X		X	X

ODI: Oswestry Disability Index; NRS: Numerical Rating Scale; GPE: Global Perceived Effect Scale; SF-12: Medical Outcome Study Short Form 12; EQ-D5: EuroQol; ÖMPSQ: Örebro Musculoskeletal Pain Screening Questionnaire; FABQ: Fear-Avoidance Beliefs Questionnaire; CEQ: credibility/expectancy questionnaire; PCI: Pain Coping Inventory; PRODISQ: Productivity and Disease Questionnaire; wk: week or weeks.

#### Prognostic factors

Prognostic factors indicating unfavourable outcome after lumbar disc surgery include length and severity of complaints preceding surgery and psychosocial factors. Complications during surgery are another prognostic factor which will be retrieved from the patient files during the 6-week assessment
[21].

#### Primary outcome measures

The recommended core set of outcomes for low back pain research
[22] will be used, and all measures are self-reported.

Functional status will be assessed by the Oswestry Disability Index (ODI)
[23,24]. The ODI consists of 10 questions assessing aspects of daily living, each being scored on a six-point scale, ranging from 0–5. The total score comprises the 10 item-scores and ranges from 0 (no difficulty) to 50 (maximal difficulty).

Pain intensity will be measured for leg pain and low back pain on an 11-point numerical rating scale (0 = no pain to 10 = worst imaginable pain)
[25,26]. Average pain intensity over the preceding week will be measured, for leg pain and low back pain separately. At three days postoperative the pain at the time of measurement will be assessed, again for leg and back pain separately.

Global perceived recovery will be evaluated with the seven-point Global Perceived Effect scale (GPE), ranging from “completely recovered” to “worse than ever”
[22]. This will be dichotomised into success (completely and much recovered) and non-success (slightly recovered, no change, slightly worse, much worse and worse than ever).

The Medical Outcome Study Short Form 12 (SF-12) will be used to assess general health status
[27,28]. The 12 items cover the dimensions physical function and mental health. Sum-scales can be derived with scores ranging from 0–100 per dimension. Higher scores reflect better health.

The EuroQol (EQ-D5) will be administered to assess health related quality of life
[29,30]. This instrument evaluates 5 dimensions of quality of life on a three-point scale (no problems, moderate problems and severe problems). Utilities based on the EQ-5D will be estimated using the Dutch valuation tariff
[31].

Costs will be measured from a societal perspective using cost questionnaires. Only costs related to leg and back pain are considered and will include costs of continued rehabilitation, other health care costs, patient and family costs, and missed days of unpaid work. The cost questionnaires and the therapists’ registrations of sessions completed are also used to check compliance to the allocated treatment and possible cross-over, i.e. receiving exercise therapy in the control group either by means of direct access or referral.

A modified version of the Productivity and Disease Questionnaire (PRODISQ) will be used to evaluate absence from paid work
[32]. Dutch standard costs will be used to value resource utilisation
[33]. Lost productivity costs will be estimated according to the friction cost approach
[34] and the human capital approach.

#### Secondary outcome measures

Expectations of treatment outcome will be measured using the credibility/expectancy questionnaire (CEQ)
[35,36]. The CEQ contains three nine-point credibility scales, two expectancy scales (0–100%) and one nine-point credibility item. Higher scores reflect more positive expectations. At baseline, expectations of surgery outcome will be elicited. Furthermore, to assess expectations regarding continued rehabilitation post-surgery and the watchful waiting policy, respectively, the reformulated CEQ item on expected success of treatment will be used. All CEQ baseline measures will be taken prior to treatment allocation. The CEQ will be used to measure expectations regarding the allocated strategy post-surgery one week postoperatively in the watchful waiting group and following the first treatment session in the continued rehabilitation group.

Psychosocial risk profiles will be measured with the Örebro Musculoskeletal Pain Screening Questionnaire (ÖMPSQ)
[37-40]. The 21 items of this questionnaire evaluate function, pain, psychological factors and fear avoidance on 11-point scales, yielding a total score range of 0–210. Higher scores indicate a higher risk of developing long-term problems.

Fear-avoidance beliefs will be measured with the Fear-Avoidance Beliefs Questionnaire (FABQ)
[41,42]. This instrument measures both fear-avoidance beliefs about work (FABW) (11 items) and about physical activity (FABPA) (5 items) using seven-point scales. Sum-scores will be calculated for FABW (7 items, range 0–42) and for FABPA (4 items, range 0–24).

Pain coping will be assessed with the Pain Coping Inventory (PCI)
[43]. The PCI comprises 33 items, evaluating three active and three passive pain coping dimensions on a four-point scale ranging from ‘seldom or never’ to ‘very often’.

### Blinding

Neurosurgeons will be blinded for group allocation, as randomisation and group allocation is performed after their involvement in participant recruitment. The research nurses will inform participants on treatment allocation and can, therefore, not be blinded. The nature of the postoperative strategies precludes blinding of the patient and the therapist. Besides, all measures are patient reported outcomes, and therefore outcome assessment is not blinded. The unequal size of intervention and control group, necessary for multilevel analysis, prevents blinding of the researcher and the statistician involved in outcome analyses.

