### Sample size

Power calculations were based on a Cochrane review assessing the effectiveness of rehabilitation following lumbar disc surgery
[18] and were performed for the three main outcomes (for all: power 0.9; alpha 0.05). To detect a clinical relevant mean difference in a multi-level analysis between the continued rehabilitation group and the watchful waiting group of 8 points on the ODI (SD 15), a total of 165 patients is needed. To detect a difference of 2 points (SD 3) for pain (11-point NRS) a total of 105 patients is needed. For detecting a 20% difference on the dichotomised global perceived recovery (recovered vs not recovered) a total of 150 patients is needed. Anticipating 15% potential study withdrawal, a total of 200 patients will be recruited. Participants will be unequally distributed (109 intervention vs. 91 control) to allow for multilevel analysis, taking into account the multilevel structure of the data in the intervention group.

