### Data analysis

Baseline characteristics in both arms will be compared to check if randomisation has resulted in an equal distribution of the main outcome measures, prognostic factors and known confounding factors such as age, gender, living status and educational level.

The primary analysis will be an intention-to-treat analysis. All continuous responses will be analysed in a linear mixed model with responses at baseline and 3, 6, 9, 12 and 26 weeks. If necessary, missing items within a questionnaire will be imputed using multiple imputation techniques. In these analyses we will take into account the levels of neurosurgeon, primary care therapists, patient and time of measurement. The effect of interest for the present study will be the time by treatment interaction. Therefore, regression coefficients with 95% confidence intervals (CI) between baseline and follow up measurements will be calculated. If appropriate, analyses will be adjusted for patient characteristics that differ between the two groups. For the dichotomous outcomes we will use a generalised mixed model (logit link) with the same multilevel structure, and the effect of interest will be the difference between groups at each time point. Odds ratios with 95% CI between intervention and control groups will be calculated.

A per protocol analysis will be performed to estimate the extent to which protocol deviations may bias the results. A protocol deviation is defined as receiving one or more sessions of exercise therapy in the first six to eight weeks after surgery in the control group, or not receiving any sessions of exercise therapy in the first six to eight weeks postoperatively by participants in the intervention group.

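### Unequal arm sizes unmask arms coded A and B, but they are not required for multilevel analysis and do not prevent blinded analytic decisions

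*Protocol article*

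**What the plan says.** The Blinding section of the protocol article states that patients, therapists and research nurses cannot be blinded and that every outcome is reported by the patient. Neurosurgeons are to be blinded. On the analysis it says: "The unequal size of intervention and control group, necessary for multilevel analysis, prevents blinding of the researcher and the statistician involved in outcome analyses".

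The Sample size section gives the split and its reason: "Participants will be unequally distributed (109 intervention vs. 91 control) to allow for multilevel analysis". The clustering it has in mind lies in one arm only, since the allocation is described as "taking into account the multilevel structure of the data in the intervention group". The section states no intraclass correlation and no design effect.

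The Data analysis section specifies mixed models with levels for neurosurgeon, therapist, patient and time. Two choices stay open there:

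- Item imputation: "If necessary, missing items within a questionnaire will be imputed using multiple imputation techniques".
- Covariates: adjustment is to be made, where judged appropriate, for patient characteristics found to differ between the arms. No rule is given for either part of that condition.

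The same section defines a protocol deviation by counting therapy sessions, separately for each arm.

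**The concern.** The sentence on analyst blinding makes two claims: that multilevel analysis requires unequal arms, and that unequal arms make it impossible to blind the researcher and the statistician. Neither holds as a general statement.

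This matters because blinding is already limited. The people who report the outcomes know their treatment. Keeping the allocation away from those who make the remaining analytic choices is a protection that is still available once data have been collected, and the article gives it up on the stated ground. The two open choices can then be made by people who can see what each option does to the treatment effect. The covariate choice bears directly on the primary estimate.

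**Working it through.** **1. Do the plan's own figures show where the split comes from?**

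Inputs from the Sample size section:

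- Error rates, the same for each main outcome: "for all: power 0.9; alpha 0.05".
- Functional status, with the difference to be detected given as: "of 8 points on the ODI (SD 15), a total of 165 patients is needed".
- Pain, with its own target and total: "To detect a difference of 2 points (SD 3) for pain (11-point NRS) a total of 105 patients is needed".
- Allowance for loss to follow-up: "Anticipating 15% potential study withdrawal, a total of 200 patients will be recruited".

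The article does not state sidedness; two-sided is assumed.

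Per arm, n = 2(1.960 + 1.282)² SD²/Δ² = 2 × 10.507 × SD²/Δ².

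- ODI: 2 × 10.507 × 225/64 = 73.9, so 74 per arm and 148 in total (stated: 165).
- Pain: 2 × 10.507 × 9/4 = 47.3, so 48 per arm and 96 in total (stated: 105).

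The plain formula misses both figures. Inflating only the intervention arm by 109/91 = 1.198 gives:

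- ODI: 74 + 74 × 1.198 = 74 + 89 = 163 (stated 165).
- Pain: 48 + 48 × 1.198 = 48 + 58 = 106 (stated 105).

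Both come close. A design effect of about 1.2 in the intervention arm is therefore a reasonable inference, but it is not a stated input. For withdrawal, 165/0.85 = 194.1, so 195, rounded up in the plan to 200. The recovery figure of 150 cannot be checked, because no base rate is given.

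**2. Does multilevel analysis need the unequal split?**

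With design effect D in the intervention arm only, the variance of the difference is proportional to D/n₁ + 1/n₀. Compared with 100:100, the ratio is (D/109 + 1/91) / ((D + 1)/100).

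| D (assumed) | 109:91 | 100:100 | Ratio |
|---|---|---|---|
| 1.0 | 0.02016 | 0.02000 | 1.008 |
| 1.2 | 0.02200 | 0.02200 | 1.000 |
| 1.43 | 0.02411 | 0.02430 | 0.992 |
| 2.0 | 0.02934 | 0.03000 | 0.978 |

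The tie at 1.2 is algebra, not chance. If n₁ = D n₀ and the total is N, then n₀ = N/(1 + D), and D/n₁ + 1/n₀ = 2/n₀ = 2(1 + D)/N. Equal arms of N/2 give (D + 1)/(N/2), which is the same value. So a split made by inflating one arm by its design effect gains nothing over equal arms with the same total.

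ODI power (8 points, SD 15, 15% loss in each arm), 109:91 against 100:100:

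- D = 1.2: 0.912 against 0.912
- D = 1.435: 0.886 against 0.883
- D = 2.0: 0.819 against 0.810

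Over this range equal arms cost between none and about one percentage point of power. The model can be fitted with either split.

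**3. Does the unequal split unmask the arms?**

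Suppose the analyst sees groups labelled A and B and guesses that the larger is the intervention arm. With independent binomial retention from 109 and 91, the guess is right with probability:

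- 100% with complete data
- 99.8% with 15% loss in both arms
- 83% with 20% loss in the intervention arm and 10% in the control arm

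The loss rates other than the stated 15% are assumptions. Therapist clustering exists only in the intervention arm, so the therapist field would also identify it. Coded-arm blinding therefore fails.

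In a file with the arm and therapist fields removed there are no groups to count. In a file with them randomly permuted, the counts 109 and 91 carry no information about any patient. Imputation rules and model code can be settled and tested on either.

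**4. What might one open choice do?**

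As an illustration only, suppose a choice yields two analyses and either may be reported if significant. P(|z₁| > 1.96 or |z₂| > 1.96) is 6.5%, 7.0% or 7.8% in place of 5% for correlations of 0.95, 0.9 or 0.8 between them. The correlations are assumed, and so is the selective reporting.

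**The case against.** The strongest reply is that the stated reason has substance. With a known 109:91 target, ordinary A/B coding is broken almost at once, and one-arm therapist clustering breaks it again. The claim of necessity can be read as shorthand for allowing for clustering in the intervention arm, which the reproduced sample sizes support. The split itself is harmless. All of this stands. It justifies saying that coded arms would be unmasked, but not that blinding is prevented.

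A second reply is that a separate analysis plan, not shown, may fix the imputation and covariate rules beforehand. That also stands, and it is why one can say only that these choices may be made with the allocation in view. A reader might infer that they will be, or that cleaning, imputation and deviation coding are all done unblinded. The Blinding section speaks only of people involved in outcome analyses and does not say so. A separate plan would still leave the published statement wrong.

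Three further inferences are not supported:

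- Analyst blinding is not the only layer left, because neurosurgeons are to be blinded too.
- Who counts as a deviator is not left to taste. The Data analysis section gives a session-count rule, and it affects only the per-protocol analysis.
- The type I error figures in the illustration do not estimate bias in this trial.

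Finally, covariates chosen because they differ between the arms cannot be chosen on a file without the arm. That objection is correct, and it means the covariate rule itself has to change.

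**Conclusion.** The point holds in a limited form. Unequal arms are an efficiency choice and not a requirement of multilevel analysis. Against 100:100, the 109:91 split changes the variance by +0.8% to -2.2% for assumed design effects of 1.0 to 2.0, and by nothing at the inferred value of about 1.2. The split defeats A/B coding (99.8% under equal 15% loss) but does not defeat blinded decisions on arm-withheld or permuted data. As published, the article gives up blinding of the researcher and statistician on too broad a ground, next to two unresolved analytic choices on self-reported outcomes.

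This is a cheap improvement to the conduct and reporting of the analysis. It is not evidence that the trial's result is or will be biased, and it is no criticism of the 109:91 allocation as such. The conclusion about precision rests on clustering being confined to the intervention arm and on the assumed design effects. The conclusion about blinding rests on neither.

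**What to change.** Delete the claim that unequal arms are needed for multilevel analysis, and replace the sentence on the researcher and statistician with a staged rule:

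1. Fix the adjustment covariates in advance on prognostic grounds, in place of choosing them from observed differences between arms.
2. Settle and test the outcome imputation rule and the model code on outcome files in which the arm and therapist identifiers are withheld or randomly permuted.
3. Have existing data staff apply the current session-count rule for the per-protocol set without access to outcome data.
4. Sign off these decisions, then merge the true allocation and run the fixed code.

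Cost items need not be removed for the cost imputation in the economic evaluation. The article can also say plainly that the known split would unmask coded arms, which is why withholding or permutation is used.

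The cost is a change of wording and a data-handling step for existing staff, with no extra patients or procedures. The drawback is slightly later access to the arm-linked file.

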### Sample size

Power calculations were based on a Cochrane review assessing the effectiveness of rehabilitation following lumbar disc surgery
[18] and were performed for the three main outcomes (for all: power 0.9; alpha 0.05). To detect a clinical relevant mean difference in a multi-level analysis between the continued rehabilitation group and the watchful waiting group of 8 points on the ODI (SD 15), a total of 165 patients is needed. To detect a difference of 2 points (SD 3) for pain (11-point NRS) a total of 105 patients is needed. For detecting a 20% difference on the dichotomised global perceived recovery (recovered vs not recovered) a total of 150 patients is needed. Anticipating 15% potential study withdrawal, a total of 200 patients will be recruited. Participants will be unequally distributed (109 intervention vs. 91 control) to allow for multilevel analysis, taking into account the multilevel structure of the data in the intervention group.

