**Methods/Design:**

A randomised controlled trial will be conducted with an economic evaluation alongside to assess the (cost-) effectiveness of rehabilitation after lumbar disc surgery. Two hundred patients aged 18–70 years with a clear indication for lumbar disc surgery of a single level herniated disc will be recruited and randomly assigned to either a watchful waiting policy for first six weeks or exercise therapy starting immediately after discharge from the hospital. Exercise therapy will focus on resumption of activities of daily living and return to work. Therapists will tailor the intervention to the individual patient’s needs. All patients will be followed up by the neurosurgeon six weeks postoperatively. Main outcome measures are: functional status, pain intensity and global perceived recovery. Questionnaires will be completed preoperatively and at 3, 6, 9, 12 and 26 weeks after surgery. Data will be analysed according to the intention-to-treat principle, using a linear mixed model for continuous outcomes and a generalised mixed model for dichotomous outcomes. The economic evaluation will be performed from a societal perspective.

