#### Follow-up consult neurosurgeon

Six to eight weeks after discharge a follow-up consult with the neurosurgeon will take place. Whether patients are referred for further treatment after this follow up consultation is left to the neurosurgeons’ discretion. We will measure all health care consumption using cost questionnaires (see section on Economic evaluation below).

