## Discussion

A systematic review that summarised results of several randomised controlled trials yielded moderate to low quality evidence for effectiveness of postoperative exercise programmes starting 4–6 weeks after first time lumbar disc surgery
[18]. Exercise programmes seem to be more beneficial than no treatment, and high intensity exercises may be more effective than low intensity exercises. Little is known about the effectiveness of immediate postoperative interventions in these patients
[18]. Besides, knowledge about cost-effectiveness of postoperative management is scarce
[19]. Therefore, the REALISE trial aims to evaluate the effectiveness of an exercise therapy intervention starting in the first postoperative week, compared to a watchful waiting policy during the first six to eight weeks after surgery. To that end we mainly focus on the question whether exercise treatment leads to a faster recovery as compared to watchful waiting during this immediate post operative period. Furthermore, cost-effectiveness will be assessed by means of an economic evaluation. Treatment in the intervention group is based on a protocol that allows therapists to provide a tailored intervention. Also, both physiotherapists and exercise therapist will deliver the treatment, as this reflects current practice in the Netherlands. This will result in a variation across treatments and will improve generalisability of the findings. The results of this trial may lead to a more consistent postoperative strategy for patients who underwent surgery for lumbar disc herniation.

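### The protocol gives three different primary outcome sets and no primary time point, and it allows each main outcome the full 0.05, so neither the 5% error rate nor the 90% power belongs to the trial's conclusion

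*Protocol article*

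**What the plan says.** The protocol article defines the primary set in three ways.

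- **Three main outcomes.** Abstract: "Main outcome measures are: functional status, pain intensity and global perceived recovery". The Sample size section agrees; its calculations "were performed for the three main outcomes (for all: power 0.9; alpha 0.05").
- **Six rows.** Under its primary heading, Table 1 lists ODI, leg pain, back pain, GPE, SF-12 and EQ-5D. The last row reads "Health related quality of life (EQ-5D").
- **Eight measures.** The section on primary outcome measures covers those six ("The Medical Outcome Study Short Form 12 (SF-12) will be used to assess general health status") and adds costs and absence from paid work. Table 1 puts these last two under the economic evaluation instead.

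Pain is scored separately for leg and back, but the Sample size section powers a single pain outcome without saying which.

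The clinical outcomes are collected at 3, 6, 9, 12 and 26 weeks. For continuous outcomes, Data analysis takes the time by treatment interaction as the effect of interest, with coefficients from baseline to the follow-ups. For dichotomous outcomes, "the effect of interest will be the difference between groups at each time point". The Discussion gives the main question as "whether exercise treatment leads to a faster recovery as compared to watchful waiting during this immediate post operative period". No section ties a particular outcome and time to that question.

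**The concern.** A reader cannot tell from this document which result decides the trial. The candidates are three, six or eight outcomes, with up to five times for each clinical one, and each main outcome was powered as if it stood alone. If any one of them can be reported as showing effectiveness, the error rate of that conclusion is above 5%. The reverse risk also exists: an early benefit could be called negative because another contrast was null.

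The Blinding section makes this more pressing. All outcomes are self-reported by unblinded patients, and neither the researcher nor the statistician is blinded. A primary contrast fixed in advance is the main safeguard against choosing a result after seeing the data.

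**Working it through.** **Inputs.** From Sample size: alpha 0.05 and power 0.90 for each main outcome; ODI difference 8, SD 15, N 165; pain difference 2, SD 3, N 105; GPE difference 20%, N 150; withdrawal 15%; total 200, split 109:91. Sidedness is not stated, so two-sided is assumed. Correlations between outcomes and between times are not given; those used below are assumptions.

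**The plan's own figures.**
- ODI, equal arms: n per arm = 2 × (1.960 + 1.282)² × (15/8)² = 73.9, so 74 per arm and N = 148. At 109:91, N = 150. The protocol states 165, and 165/150 = 1.10.
- Pain, equal arms: 2 × (1.960 + 1.282)² × (3/2)² = 47.3, so N = 96 (97 at 109:91), against 105 stated.
- Both stated figures are about 8–12% above the simple formula. That fits an unstated allowance for clustering and does not show an error.
- GPE: the base rate is not stated. Control rates of 46–75%, the early recovery range in the Background, give N between 130 and 277 depending on continuity correction. The stated 150 lies inside that range.
- Withdrawal: 165/0.85 = 194.1, so 195, consistent with 200.

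Each calculation is for one outcome at one unnamed time, at the full 0.05.

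**Chance of at least one false positive, each test at 0.05.** If independent, this is 1 − 0.95^k. The correlated cases come from simulated normal test statistics.

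| Family | Independent | Correlated (assumed) |
|---|---|---|
| 3 main outcomes, one time | 1 − 0.95³ = 14.3% | about 12% at 0.5 |
| 4 variables (leg and back pain separate), one time | 1 − 0.95⁴ = 18.5% | about 16% at 0.5 |
| 3 main outcomes, five times tested separately | 1 − 0.95¹⁵ = 53.7% | 32–38% (outcomes 0.5–0.6, times 0.6–0.7) |

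With a wider range of correlations (outcomes 0.3–0.7, times 0.5–0.8) the last row runs from 26% to 44%. Every case is above 5%.

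**Cost of correcting for four variables at one time.** Evaluable patients: 200 × 0.85 = 170, split 92.65 and 77.35 at 109:91. The first Holm step uses 0.05/4 = 0.0125, critical value 2.498.
- Without inflation: SE = 15 × √(1/92.65 + 1/77.35) = 2.310 and 8/2.310 = 3.463. At 0.05: 3.463 − 1.960 = 1.503, power 0.93. At 0.0125: 3.463 − 2.498 = 0.965, power 0.83.
- With the implied inflation of 1.10: SE = 2.310 × √1.10 = 2.423 and 8/2.423 = 3.302. At 0.05: 3.302 − 1.960 = 1.342, power 0.91. At 0.0125: 3.302 − 2.498 = 0.804, power 0.79.

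**The case against.** Multiplicity rules are commonly left to a statistical analysis plan, and that plan is not shown. This stands for the correction method. It does not excuse a protocol that labels its primary set in three ways: an analysis plan would first have to choose among them.

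The Abstract and Sample size section do agree on three main outcomes, and the Discussion does point to the early period. So the intent is partly visible. What is missing is the link from that intent to one contrast.

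The time multiplicity depends on how Data analysis is read. One interaction test per continuous outcome would remove it for everything except GPE, which is compared at each time. GPE alone over five times gives about 15% at time correlation 0.7 and 18% at 0.5. Such a test would also not isolate early recovery.

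Some stronger readings are tempting but not supported.

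- **Late contrasts as invalid.** Because "Whether patients are referred for further treatment after this follow up consultation is left to the" neurosurgeon, a reader might infer that the 9–26 week results no longer compare the two policies. The Background, however, defines watchful waiting as including treatment after six to eight weeks for persisting symptoms. The late contrasts are valid strategy comparisons; they simply do not answer the early-recovery question.
- **Eight measures at five times.** Costs and work absence are collected only at 6, 12 and 26 weeks, and the economic section plans no significance test on them. Alpha 0.05 is explicit only for the three main outcomes; for SF-12 and EQ-5D it can only be inferred from the 95% intervals. Error rates of 50–60% need seven variables tested separately at every time.
- **A joint interaction test as badly underpowered.** Power of 0.70 on 5 degrees of freedom is a floor, reached only for special effect patterns. A constant effect or a 6-week-only effect gives 0.83–0.99.

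**Conclusion.** The concern holds in this form: the primary set is stated inconsistently, no primary time point is named, and the full 0.05 is given to each main outcome with no rule for combining them. The nominal 5% and 90% therefore apply to one contrast and not to the trial's conclusion.

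The smallest consequence is a 12–14% chance of a false positive (three outcomes, one time). It is about 32–38% if three outcomes are tested separately at five times. These figures assume that any single success could be reported as effectiveness, and the correlated ones rest on assumed correlations. A rule that all three outcomes must succeed would not inflate the error rate, but none is stated.

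The point does not depend on the sample size being wrong. The 165 could not be reproduced because the clustering inputs are not given, and that alone shows no fault.

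That ÖMPSQ, FABQ and PCI stand under secondary outcomes in Table 1 (for example "Fear avoidance beliefs (FABQ")) while being measured only at baseline is a minor labelling slip. It affects no treatment comparison.

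**What to change.** 1. Make the Abstract, Table 1, the primary outcome section and the Sample size section agree on one primary set. Say whether pain means leg, back or both.
2. Name one early primary time point, such as the 6-week assessment. When choosing it, reconcile the timing of the neurosurgeon's follow-up, which is six weeks after surgery in the Abstract and six to eight weeks after discharge in the section on that consult.
3. Then choose one of two routes; which outcome leads is the sponsor's decision.
   - **One primary outcome.** ODI is an example, since it drives the sample size. Alpha stays 0.05 and N stays 165/200.
   - **Several primary outcomes.** Keep ODI, leg pain, back pain and GPE, with Holm at that time point. State the cost: first-step ODI power of about 0.79 instead of 0.91 at 170 evaluable with the implied inflation, or 0.83 instead of 0.93 without it.
4. Label SF-12, EQ-5D, costs and work absence as secondary or economic outcomes, and report the 9–26 week contrasts as secondary strategy comparisons.
5. As a tidy-up, move ÖMPSQ, FABQ and PCI to the baseline prognostic factors.

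The single-outcome route changes wording only. Because the protocol is registered and has ethics approval, either route needs a documented amendment, made before anyone looks at comparative data.
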